### Sample size

The primary outcome is the proportion of patients achieving a 14 day pain score of less than 4 out of 10 (from a baseline score greater than or equal to 7 out of 10). A sample size of 60 patients per arm will have >80% power and 95% confidence to detect a difference in this primary outcome from 35% in the control arm to 65% in the active arm, allowing for a modest loss to follow-up. Recruitment is expected to start November 2011 and take approximately 3 years.

### Analysis

Effectiveness analyses will be by the intention-to-treat principle, whereby patients are analysed according to the study arm to which they were randomized regardless of the treatment actually received, and toxicity analyses will be according to treatment received. Proportions will be compared using a two-sided chi-squared or exact (conditional binomial) test. Changes in quality of life measures (pain and functional disability scores) will be analysed using *t*-tests to enable comparisons with published studies, and non-parametric tests or regression modelling techniques depending on the distribution of the data. All comparisons will be two-sided with a significance level of 5% considered as being statistically significant. Measures of effect will be presented as either risk differences, odds ratios or mean differences together with the respective 95% confidence intervals.

The primary end point is the proportion of patients whose NRS pain score reduces from 7/10 (or more) to 4/10 (or less) at 14 days. The study sample size is sufficient to detect an absolute difference of 30% in favour of the vertebroplasty arm. Sub-group analysis will also be performed on three different regions of the spine: thoracic (T4 to T10), thoraco-lumbar (T11 to L2) and lumbar (L3-L5). Those patients with two acute fractures involving more than one of these regions will be excluded from this sub-group analysis. We hypothesize that the vertebroplasty efficacy will be maximal in the thoracolumbar group. We expect the benefit will be greater in thoraco-lumbar fractures than in thoracic and lumbar fractures. We hypothesize that the primary end point (pain score <4/10 at 2 weeks) will be achieved in more than 30% additional patients (than control) in the thoraco-lumbar fractures and in less than 30% additional patients (than control) in the thoracic group and the lumbar group. Note that the trial is not specifically powered for this sub-group analysis, and the statistical conclusions that can be drawn from the sub-group analysis will be limited by the number of patients in each sub-group.

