## Methods/design

### Trial design

The trial is a participant and outcome-assessor blinded randomized controlled trial of vertebroplasty for acute fractures. Acute fracture will be defined as new severe onset of back pain (of less than 6 weeks duration) associated with magnetic resonance imaging (MRI) or single-photon emission computed tomography (SPECT)-computed tomography (CT) evidence consistent with a recent fracture. MRI or SPECT-CT must be obtained within a week of patient enrolment. The MRI will include sagittal T1 weighted and fat suppressed T2 weighted images of the thoracic and lumbar spine. Deformity of the vertebral body associated with the high signal pattern (T2) and low signal pattern (T1) of acute fracture within the vertebral body will define recent fracture. Note that the precise duration of fracture is defined by careful questioning of the patient as to the date of onset of severe pain. The pain location should be consistent with the recent fracture identified on MRI. When MRI is contraindicated, then SPECT-CT will be obtained. Increased radioisotope uptake in the pattern of recent fracture associated with fracture deformity of the vertebral body will be accepted as evidence of recent fracture.

The trial is of essentially similar design as the previous two blinded RCTs [1,2]. It is a multicentre trial involving four centres in Sydney, Australia that have established vertebroplasty programs. Data will be collected at baseline, 3 days, 2 weeks, 1 month, 3 months and 6 months post intervention. The patient and the data collectors remain blinded for the duration of the trial.

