### Random allocation

The subjects will be randomized to either the control intervention group or the vertebroplasty group using the method of minimization. This will be performed centrally at the National Health and Medical Research Council (NHMRC) Clinical Trials Centre, University of Sydney. The call to the NHMRC Clinical Trials Centre will be made once the patient is in the procedure room immediately prior to the procedure.

Randomization will be 1:1 to each treatment arm, and patients will be stratified by the following factors: * Age (<75, ≥75 years) * Degree of bone height loss (<50%, ≥50%) * Fracture due to trauma (Yes, No) * Patient taking steroids (Yes, No) * Hospital/site.

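### The primary proportion is tested without the five minimisation factors, and chi-squared and exact tests are both left open: a conservative, not invalid, analysis that costs little to sharpen

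*Protocol article*

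**What the plan says.** Under Random allocation, the protocol article allocates 1:1 "using the method of minimization" and adds that "patients will be stratified by the following factors": age, degree of bone height loss, fracture due to trauma, steroid use and hospital/site. Trial design gives four centres, so there are four two-level factors and one four-level factor.

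Under Analysis, the rule for binary outcomes is "Proportions will be compared using a two-sided chi-squared or exact (conditional binomial) test". No covariates are named, and nothing says when each test applies. Regression is mentioned only for the pain and disability scores, where the distribution of the data decides its use. The primary end point is the proportion of patients whose pain score falls to the target level at 14 days, so the quoted sentence governs it. Sample size claims more than 80% power with 60 per arm for 35% versus 65%, two-sided 5%.

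**The concern.** Minimisation is worth doing only if the factors are thought to predict outcome. If they do, balancing them makes the difference in proportions vary less from trial to trial than simple randomisation would. A plain two-by-two test does not know this. It uses the larger variance, so its confidence interval is too wide, its true error rate lies below 5%, and some power is given away.

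The second part needs no assumption about prognosis. The chi-squared and conditional exact tests do not have the same rejection region. With both named and no rule for choosing, a borderline primary result could be significant under one and not under the other. The trial is meant to settle conflicting evidence, so its main verdict should not rest on a choice that can be made after the data are seen.

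**Working it through.** **Inputs from the protocol article.** 60 per arm; 35% versus 65%; two-sided 5%; minimisation on five factors; four sites. Loss to follow-up is called modest, without a figure.

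**Assumptions, because the article gives no figures.** An 80% biased coin; two-level factor prevalences of 60, 30, 40 and 20%; site shares of 50, 20, 20 and 10%; and a common odds ratio (OR) per two-level factor of 1, 1.5, 2 or 3, with site effects scaled to match.

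**Step 1: reproduce the stated power.**
- Null standard error: √(0.5 × 0.5 × 2/60) = 0.0913.
- Alternative standard error: √(2 × 0.35 × 0.65/60) = 0.0871.
- Power: Φ[(0.30 − 1.96 × 0.0913)/0.0871] = Φ(1.39) = 91.8%.
- 80% power needs 43 per arm, or 49 with continuity correction. Sixty therefore leaves room for a loss of 17/60 = 28% or 11/60 = 18%. The claim of more than 80% is correct.

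**Step 2: ignore the factors after minimisation.** Simulated under the null at 35%, 120 patients, 4,000 trials per row. The adjusted analysis is a linear-regression risk difference on all five factors.

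| OR per factor | Mean unadjusted SE | True SD | Ratio | Type I, chi-squared | Type I, adjusted |
|---|---|---|---|---|---|
| 1 | 0.0865 | 0.0868 | 1.00 | 5.2% | 5.1% |
| 1.5 | 0.0864 | 0.0855 | 1.01 | 4.8% | 5.3% |
| 2 | 0.0863 | 0.0809 | 1.07 | 3.7% | 5.0% |
| 3 | 0.0864 | 0.0788 | 1.10 | 3.3% | 5.3% |

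As an analytic cross-check, a standard error too wide by ratio r gives size 2[1 − Φ(1.96r)]. For r = 1.011, 1.067 and 1.096 this is 4.8%, 3.7% and 3.2%, in line with the simulation. Monte Carlo error at 5% is √(0.05 × 0.95/4000) = 0.3 points.

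**Step 3: power at the design difference.** 2,500 simulated trials per cell, 35% versus 65%, shown as chi-squared / adjusted. The 102-patient column represents an assumed 15% loss (0.85 × 120), run as a trial of 102.

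| OR per factor | 120 patients | 102 patients |
|---|---|---|
| 1 | 92.6 / 91.7% | 88.4 / 85.9% |
| 1.5 | 92.6 / 92.7% | 88.4 / 87.5% |
| 2 | 93.0 / 94.0% | 90.0 / 90.6% |
| 3 | 94.6 / 96.8% | 91.2 / 93.9% |

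Adjustment gains up to about 3 points if the factors are strong and loses up to about 2.6 if they are irrelevant.

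**Step 4: the open choice of test, by exact enumeration.** No prognostic assumption enters here.

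| Per arm | Rates | Chi-squared | Exact | Gap |
|---|---|---|---|---|
| 60 | 35 v 35% (size) | 5.0% | 3.1% | 2.0 |
| 60 | 35 v 65% | 92.3% | 89.2% | 3.1 |
| 60 | 35 v 60% | 80.3% | 74.7% | 5.6 |
| 60 | 35 v 55% | 61.3% | 54.0% | 7.3 |
| 54 | 35 v 65% | 87.6% | 83.1% | 4.5 |
| 48 | 35 v 65% | 85.3% | 79.9% | 5.4 |

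A concrete case is 21/60 versus 32/60. The pooled proportion is 53/120 = 0.4417, and z = 0.1833/√(0.4417 × 0.5583 × 2/60) = 2.02. This gives p = 0.043 by chi-squared and 0.066 by Fisher's exact test. At the planned rates the smallest cell averages 60 × 0.35 = 21, so small counts give no reason to use the exact test.

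**The case against.** The strongest reply has four parts.

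- **Scope.** This is a condensed article with no analysis plan shown, and covariate adjustment and the choice between standard tests are often settled there. That would dispose of an omission. Here, though, the article states an analysis for proportions, and that statement is what is questioned. An analysis plan could still narrow it.
- **Generic wording.** The sentence covers every proportion, including sparse safety and subgroup counts, and a reader would usually take the exact test as the small-cell fallback. That is a fair reading, and it is why the exact test should stay available for those outcomes. The text does not say so for the primary end point.
- **Validity.** An unadjusted test after minimisation does not inflate false positives. This stands in full.
- **Prognosis is unknown.** This also stands. A reader might infer that standard errors are certainly too wide and power certainly lost. The documents do not support that, because they give no prognostic strength for any factor. With weak factors the effect is negligible, and with irrelevant ones adjustment costs a little power.

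Two further inferences should be resisted. The first is that the sample size is inadequate: unadjusted chi-squared power exceeded 80% in every case examined. The second is that two effect scales compete for the primary end point. The sentence "Measures of effect will be presented as either risk differences, odds ratios or mean differences" is a general list for all outcomes, and for the primary end point the Analysis section speaks of an absolute difference.

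**Conclusion.** The point holds as a moderate matter of efficiency and pre-specification, not as an error of validity. The stated primary test does not use the factors the trial balances on. Its cost ranges from nothing, if the factors are weak, to a test run at about 3-4% instead of 5% and about 1-3 points of power at the 30-point design difference, if every factor has an odds ratio of 2-3. Those figures rest on the assumed coin, prevalences and site shares. The direction, conservative or neutral, does not.

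The unresolved choice of test is firmer, since it follows from the planned rates and sample size alone: 3.1 points of power at 60 per arm, and more with losses or a smaller true difference. The stated power above 80% is confirmed at 60 per arm with either test. The only design-difference case computed below it is the exact test at 48 per arm (79.9%), a 20% loss.

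**What to change.** - Make the primary analysis a risk difference with 95% confidence interval adjusted for the five minimisation factors, for example by logistic regression with standardisation. State in advance how small sites are pooled.
- Keep the unadjusted chi-squared test as the sensitivity analysis.
- Reserve the exact test for sparse secondary and safety proportions, and say so.
- Baseline pain score may be added as a covariate. Its gain is uncertain, because entry is limited to severe pain and so restricts its range.

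The cost is a change of wording before unblinding and a little more analysis work. The factors are already recorded, since allocation uses them. The statistical downside is up to about 3 points of power if no factor is prognostic, possibly somewhat more with a conservative robust standard error. The simulations used linear regression with a model-based standard error, so the recommended estimator should be checked in the same way before it is fixed.

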## Discussion

Although the majority of osteoporotic fractures cause minimal morbidity, there is a sub-group of patients that experience severe pain or immobility. This can be a turning point in the life of an elderly patient and can be the difference between independence and institutionalized care. This patient group may develop complications from conservative therapy. Such complications could include narcotic-induced delirium, narcotic-induced constipation, loss of confidence in mobilizing after prolonged bed rest and swelling in the lower legs due to prolonged sitting with the legs not elevated. The principle of acute intervention is to break this downward spiral and allow early mobilization, earlier rehabilitation and recovery of independence.

There are several difficulties in conducting a randomized controlled procedural trial in an elderly population with acute pain. The primary end point of this trial is the numeric rated pain score at 2 weeks. Patient-rated pain score is subjective and can be affected by other factors, particularly the use of narcotic analgesics. For this reason, the trial includes two office visits (at 2 weeks and 6 months, respectively). These visits allow for the collection of a properly performed visual analogue pain score to supplement and compare with the numeric pain score. The office visits do make the trial more difficult to conduct as elderly patients with osteoporotic fractures often have difficulty arranging transportation and require family members, often at their inconvenience, to accompany them.

The Roland Morris Disability score will provide important data as it comprises 24 yes/no questions relating to low back pain and disability. This measure is regarded by the authors as of equal importance to the pain measures. The disability caused by painful spinal fractures is of just as much clinical importance as the pain itself and the 24 yes/no questions are perhaps less subjective than the simple nomination of a pain score. Analgesic use and duration of hospitalization will also provide objective although indirect measures related to pain and disability.

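### The score outcomes are planned as t-tests on change from baseline, with no commitment to a baseline-adjusted lead analysis although the baseline values are collected

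*Protocol article*

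**What the plan says.** The Analysis section of the protocol article states that "Changes in quality of life measures (pain and functional disability scores) will be analysed using" t-tests, whose purpose is "to enable comparisons with published studies". To these it adds "non-parametric tests or regression modelling techniques depending on the distribution of the data". It names no covariates and does not say which result leads.

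The same section sets one error rule for everything: "All comparisons will be two-sided with a significance level of 5% considered as being statistically significant". It also promises effect measures with 95% confidence intervals.

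The primary endpoint is handled separately. It is a binary response on the numeric pain scale (NRS) at 14 days, and "Proportions will be compared using a two-sided chi-squared or exact (conditional binomial) test".

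The Baseline assessment section and Table 2 show that NRS, visual analogue pain (VAS), RDQ, QUALEFFO and EQ-5D are all recorded at baseline. The Random allocation section lists the minimisation factors as age, bone height loss, trauma, steroid use and site. Baseline pain and baseline disability are not among them. The Discussion says of the RDQ: "This measure is regarded by the authors as of equal importance to the pain measures".

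**The concern.** A t-test on change fixes the slope of follow-up on baseline at 1. Patients enter at or near their worst pain, so the true slope may well be lower, and subtracting the whole baseline value then adds noise. ANCOVA estimates the slope from the data, and in large samples its variance is never greater than that of the change score.

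Because baseline pain and disability are not balanced by design, the arms can differ on them by chance. An arm that starts worse then tends to show more improvement on the change score for reasons unrelated to treatment. Regression is allowed, but its use depends on the distribution of the data, and that is not the reason to adjust for baseline. At stake is the precision of the secondary results, above all the RDQ, to which the authors give as much weight as to pain.

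Separately, one 5% threshold for all comparisons, with no ranking, means that some isolated significant secondary results are to be expected by chance.

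**Working it through.** **The plan's own figure.** The Sample size section says "A sample size of 60 patients per arm will have >80% power and 95% confidence to detect a difference" in the response proportion "from 35% in the control arm to 65% in the active arm". With a pooled-variance two-sided 5% test, 80% power needs 43 per arm, and 60 per arm gives 91.8%. With 10% loss (54 per arm) power is 88.8%, and with 20% loss (48 per arm) it is 84.8%. The statement reproduces. It concerns the binary primary endpoint only.

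**Precision of the scores.** Let s0 and s1 be the baseline and follow-up SDs and r their correlation. The documents give none of these, so all values below are assumptions. The NRS case uses a small s0 because Table 1 admits only pain above 7/10.

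- Variance ratio, ANCOVA to change: s1²(1 − r²) / (s0² + s1² − 2·r·s0·s1). With equal SDs this is (1 + r)/2.
- Confidence interval (CI) width on change relative to ANCOVA: 1/√ratio.
- Power on change for an effect with 80% power under ANCOVA: Φ(2.80·√ratio − 1.96).

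| Assumed case | r | Variance ratio | Saving | CI width on change | Power on change |
|---|---|---|---|---|---|
| Equal SDs | 0.3 | 1.3/2 = 0.65 | 35% | ×1.24 | 62% |
| Equal SDs | 0.6 | 1.6/2 = 0.80 | 20% | ×1.12 | 71% |
| RDQ, SD 5 then 6.5 | 0.3 | 38.45/47.75 = 0.805 | 20% | ×1.11 | 71% |
| RDQ, SD 5 then 6.5 | 0.5 | 31.69/34.75 = 0.912 | 9% | ×1.05 | 76% |
| NRS, SD 1 then 2.8 | 0.1 | 7.76/8.28 = 0.937 | 6% | ×1.03 | 77% |
| NRS, SD 1 then 2.8 | 0.3 | 7.13/7.16 = 0.996 | 0.4% | ×1.00 | 80% |

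**Chance imbalance.** The slope is b = r·s1/s0. A baseline difference D between arms shifts the change-score comparison by (b − 1)·D. For the RDQ case b is 0.3 × 1.3 = 0.39 to 0.5 × 1.3 = 0.65, so a one-point baseline difference shifts the result by 0.61 to 0.35 points, in favour of the arm that started worse. With 60 per arm the SD of D is 5 × √(2/60) = 0.91 points, so a one-point difference would not be unusual. ANCOVA removes this shift.

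**Number of comparisons.** Follow-up assessments in Table 2: NRS 5, RDQ 5, EQ-5D 5, QUALEFFO 3, VAS 2, physician VAS 2, timed up and go 2, which makes 24. Expected false positives if every null is true: 24 × 0.05 = 1.2, of which about half (0.6) would favour vertebroplasty. The chance of at least one is 1 − 0.95²⁴ = 70.8% if the tests are independent, and 60% down to 31% if the test statistics have a common correlation of 0.3 to 0.7.

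**Choice of test by distribution.** In null simulations (6,000 runs, 60 per arm), letting a normality check pick between the t-test and Mann-Whitney gave a type I error of 5.5% for normal data, 5.0% for NRS-like change and 5.2% for skewed data. Reporting whichever of the two p-values was smaller gave 6.5%, 5.7% and 7.3%. Taking the smallest of t-test, Mann-Whitney and ANCOVA, simulated for normal data, gave 8.4%.

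**The case against.** The strongest reply is that the article condenses a fuller plan. Covariates, lead models and the ordering of secondary tests are normally settled in a statistical analysis plan, which may exist and is not shown. Regression is already permitted, so the loss of precision is a risk and not a certainty. The largest saving assumes equal SDs, no SD or correlation comes from the documents, and for NRS pain there is almost nothing to gain. All of this stands, and it limits the size of the point. It does not remove it: the article names t-tests on change as the analysis of the scores, and makes any alternative depend on distributional shape.

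A reader might infer that choosing the test by distribution inflates false positives. The text does not support that. The t-test is fixed for comparability, the other method is additional, and selection by distribution keeps the error at about 5.0-5.5%. Inflation appears only if the most favourable p-value is reported, which the protocol does not provide for.

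A reader might also count some 90 comparisons by including every sub-score and drug category. That goes beyond the scores named in the sentence at issue. Nor does the Discussion's remark on the RDQ make it a co-primary outcome; it is a statement about clinical importance.

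**Conclusion.** The point holds as an avoidable weakness in the analysis of the continuous secondary scores. The stated analysis is a t-test on change, and the text commits to no baseline-adjusted analysis. Under the assumed values, adjustment would reduce variance by about 9-20% for the RDQ, by 20-35% for a score with equal SDs and correlation 0.6 down to 0.3, and by 0-6% for NRS pain. For the RDQ this means confidence intervals about 5-11% wider than they need be. The shift from a chance baseline difference is an error given the imbalance that occurs; over repeated randomisations the change score is unbiased.

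The blanket 5% rule is a lesser point: about 1.2 false positives are expected over 24 main score comparisons under the null. Neither point touches the primary endpoint, a single binary outcome at day 14 with its own test. It would be wrong to conclude that the trial's main claim is at risk.

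**What to change.** - For each continuous score, name one lead analysis: ANCOVA at the visit of interest, or a mixed model over the follow-up visits, adjusted for the baseline value and the minimisation factors. Use robust or bootstrap confidence intervals if the data are skewed.
- Keep the t-test on change as a supportive analysis, labelled as being for comparison with published studies.
- State that secondary results are supportive estimates with 95% confidence intervals unless a testing order is pre-specified. Whether to set an order, and which outcome should head it, is for the investigators to choose.

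If an analysis plan already says this, it need only be cited. Otherwise the cost is a few sentences, fixed before the allocation is unblinded, and no new data. The trade-off is that secondary results outside a pre-specified order could not be presented as confirmatory.

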**Table 2 Tab2:** **Schedule for data collection**

**Evaluations**	**Visit baseline**	**Phone day 3**	**Visit day 14**	**Phone 1 month**	**Phone 3 month**	**Visit 6 month**
Procedure/operative information	X					
Pain NRS Questionnaire	X	X	X	X	X	X
Pain VAS Questionnaire	X		X			X
Physicians VAS Questionnaire	X		X			X
Roland-Morris Low Back Pain and Disability Questionnaire	X	X	X	X	X	X
Osteoporosis Quality of Life Questionnaire (QUALEFFO)	X		X	X		X
EQ-5D Questionnaire	X	X	X	X	X	X
Change in pain		X	X			
Perception of treatment assignment		X	X			
Pain medication	X	X	X	X	X	X
Timed up and go test	X		X			X
Adverse events		X	X	X	X	X
Resource use/health care utilization information						X
Erect spinal X-ray	X					X

The numeric rated scale (NRS) of pain will be used at all data collection points. Patients will be asked to answer with a number between 0 to 10 to estimate their pain intensity. This is the primary outcome measure. To standardize results, the primary pain question is the same as that used in the INVEST Trial [16], the larger of the published blinded trials of vertebroplasty. This primary pain score will record pain over the previous 24 hours. Separate numeric pain scores at rest and during standing or moving will also be obtained.

Visual analogue scale (VAS) of pain will be recorded at the three clinic visits (baseline, 2 weeks and 6 months post procedure). This score will be obtained by asking the patient to make a mark on a line which is 10 cm in length in answer to the primary pain question. The line is marked “no pain” at the left extreme and “worst possible pain” at the right extreme. There are no other divisions or marks on the line. This VAS measure is recorded for overall pain over previous 24 hours as well as separate measures for pain at rest and during walking or activity. This VAS pain score will supplement the NRS pain score at these three time points including the primary end point (NRS pain at 2 weeks post procedure). The subjective nature of patient reported pain is problematic and thus the dual pain measurements. The researcher will also record their own estimate of patient pain at the clinic visits.

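### The primary endpoint carries two incompatible success cut-offs, 14-day NRS below 4 and NRS 4 or less, so one data set can be significant under one and not under the other.

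*Protocol article*

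**What the plan says.** Protocol article, Sample size: primary success is measured by "the proportion of patients achieving a 14 day pain score of less than 4 out of 10", among patients who start at 7 or higher. The planning rates of 35% (control) and 65% (active), and the 60 patients per arm, are attached to this definition.

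Protocol article, Analysis, where the primary endpoint is formally stated: the proportion of patients whose NRS "reduces from 7/10 (or more) to 4/10 (or less) at 14 days".

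Protocol article, Analysis, same paragraph, in the sub-group hypothesis: "primary end point (pain score <4/10 at 2 weeks".

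Two other places name the endpoint without a cut-off. The text under Table 2 has "primary end point (NRS pain at 2 weeks post procedure", and the Discussion has "The primary end point of this trial is the numeric rated pain score at 2 weeks".

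The baseline half of the endpoint also varies. Sample size and Analysis use 7 or more, while the Background and the inclusion criteria in Table 1 require a score above 7.

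**The concern.** The NRS is answered with a number from 0 to 10, so a patient can score exactly 4. That patient is a failure under the Sample size definition (0-3) and a success under the Analysis definition (0-4). Both sentences carry the label of primary outcome or primary endpoint, and the article gives no rule of precedence.

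At stake is the trial's one confirmatory test. An analyst could cite the published protocol for either cut-off, and whichever is reported could be challenged as chosen after the results were known. The stated rates of 35% and 65% also describe only the below-4 proportion.

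**Working it through.** **1. The plan's own figure.** Inputs from Sample size, Analysis and Random allocation: p1 = 0.35, p2 = 0.65, n = 60 per arm, two-sided 5%, 1:1.

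Power = Φ{[|p2 − p1|·√n − 1.96·√(2·p̄(1 − p̄))] / √(p1(1 − p1) + p2(1 − p2))}, with p̄ = 0.50.

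= Φ{[0.30·7.746 − 1.96·0.7071] / 0.6745} = Φ(1.39) = 91.8%.

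Full enumeration gives 92.3% (uncorrected chi-squared) and 89.2% (Fisher). 80% power needs 43 per arm, or 49 with continuity correction, so 60 leaves room for (60 − 43)/60 = 28% or (60 − 49)/60 = 18% loss. The claim of more than 80% power is reproduced for the below-4 endpoint.

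**2. Can the cut-off alone change the verdict?** Hypothetical data, 60 per arm, control versus active:

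| Score <4 | p (chi-squared; Fisher) | Exactly 4 | Score ≤4 | p (chi-squared; Fisher) |
|---|---|---|---|---|
| 21 vs 33 | 0.028; 0.043 | 8 vs 4 | 29 vs 37 | 0.142; 0.199 |
| 21 vs 30 | 0.097; 0.139 | 3 vs 9 | 24 vs 39 | 0.006; 0.010 |
| 21 vs 33 | 0.028; 0.043 | 6 vs 6 | 27 vs 39 | 0.028; 0.043 |

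First row: the pooled rate is 54/120 = 0.45, SE = √(0.45·0.55·2/60) = 0.0908, z = 0.20/0.0908 = 2.20. Under ≤4 the pooled rate is 66/120 = 0.55, the SE is the same, and z = 0.1333/0.0908 = 1.47. The verdict can move either way. The third row shows that equal numbers scoring 4 in both arms can leave it unchanged.

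**3. How often?** The share scoring exactly 4 is not in the article, so it is modelled. Assume a latent normal score rounded to whole numbers, SD σ from 2.0 to 3.0, with the mean set so that a proportion p scores below 4: μ = 3.5 − σ·Φ⁻¹(p). Then P(score = 4) = Φ((4.5 − μ)/σ) − p.

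For σ = 2.5, control: μ = 4.46, P(≤4) = 0.506, P(=4) = 0.506 − 0.35 = 0.156. Active: μ = 2.54, P(≤4) = 0.784, P(=4) = 0.784 − 0.65 = 0.134. Expected number scoring 4: 60·(0.156 + 0.134) ≈ 17 of 120.

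Across σ = 2.0 to 3.0, 11-20% of each arm score exactly 4 (about 15-21 of 120 patients), and the ≤4 success rates are about 48-55% versus 76-81%.

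Simulated trials of 60 per arm, chi-squared test, across the same σ range:

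| Quantity | Result |
|---|---|
| Cut-offs disagree on significance, 35% vs 65% | about 8-11% |
| Same, true difference 15-20 points | about 21-26% |
| Power at 35% vs 65%, <4 | about 92% |
| Power at the same truth, ≤4 | about 90% |
| Type I error if either cut-off could be picked (35% in both arms) | about 8-9% |

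**4. Sensitivity to the model.** Apply the step 1 formula to ≤4 with freely chosen shares scoring 4 (control/active). Shares of 10%/10% give rates of 45% vs 75% and power of 92.8%; 15%/5% gives 50% vs 70% and 61.1%; 5%/15% gives 40% vs 80% and 99.7%.

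**The case against.** Four stronger readings are tempting, and the document does not support them.

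*A third definition, the score itself.* A reader might infer from the Measures text and the Discussion that mean NRS is a rival primary endpoint. Those sentences identify the instrument and the time point: one explains at which visits the VAS supplements the NRS, the other discusses the subjectivity of pain ratings. Neither says that means are compared. Both sections that define the endpoint use a proportion, and Analysis lists pain-score changes separately from proportions. This is probably shorthand that needs tidying.

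*Opposite results.* A reader might take the two rules to give reversed effects. What is shown is a change between significant and not significant. At the planned effect, the cut-offs agree in about nine trials out of ten.

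*An invalid sample size.* The 35% and 65% rates do belong to the below-4 rule, but under the rounded normal model power for 4-or-less is still about 90%. It falls materially only if exact 4s are much more common in controls, as in the 15%/5% case, and nothing in the article suggests that.

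*A 5% error rate already lost.* The 8-9% holds only if the analyst sees both results and reports the favourable one. The article shows no such intent, and the analysis plan is not shown. The figure measures the opportunity that the ambiguity leaves open.

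The core conflict survives all four points. It lies in current text, is spelled out in words as well as symbols, and cannot be put down to condensation, because the article states the endpoint twice in incompatible terms. An analysis plan that adopted either cut-off would contradict a sentence of this protocol.

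**Conclusion.** The concern holds for the two cut-offs, below 4 and 4 or less. A score of exactly 4 is classified both ways, and the significance of the primary comparison can turn on it. The frequencies (8-11% at the planned effect, 21-26% at a 15-20 point difference, 8-9% type I error under after-the-fact choice) rest on a rounded normal NRS with SD 2.0 to 3.0 and 60 analysed per arm. The contradiction itself rests on no assumption. The sample size stands as calculated for the below-4 endpoint. Because the defect touches the single confirmatory test and can be removed by wording alone, it should be corrected before unblinding.

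**What to change.** Before unblinding, state one definition in every section. Success as a 24-hour NRS below 4 (0-3) at day 14 is the natural choice: the sample size and its planning rates rest on it, and the sub-group hypothesis already uses it. Then:

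- Correct the Analysis sentence that allows a score of 4, and report 4-or-less only as a labelled sensitivity analysis.
- Clarify in the text under Table 2 and in the Discussion that the primary endpoint is the proportion, with the NRS at 2 weeks as the measure behind it.
- Reconcile the baseline threshold in the endpoint (7 or more) with the entry criterion (above 7) in the Background and Table 1.

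The cost is a wording change in the protocol, mirrored in the analysis plan. It needs no patients, no new data and no new sample size. Time is short: the article reports 112 enrolled at 5 September 2014 and expects enrolment to end in December 2014.
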